#### Outcome measures

The primary outcome is effectiveness of the implementation strategy, which is defined as the observed increase in adherence to the developed quality indicators with regard to the chosen target group (for example non-progressing labour or previous CS) between the intervention and control hospitals and the actual CS rates in both groups. Secondary outcome measures are experiences and satisfaction of healthcare providers and patients with the implementation strategy as well as applicability and costs.

#### Sample size considerations

For a sample size calculation, the target group and the adherence to the quality indicators regarding this target group are necessary. These data will be available after performing the current care as well as the barrier study. Based on these data, the sample size can be calculated. In this calculation, we will take into account clustering of patients within professionals and hospitals. We expect most of the clustering at professional level and presume an inclusion of a number of professionals per hospital and a number of patients per professional. For pragmatic reasons, we will include at most 12 out of the 20 hospitals of the current care measurement. This sample of hospitals has to be representative for the Dutch setting, *i.e.*, a total of two university hospitals, six non-university teaching hospitals, and four non-university, non-teaching hospitals.

#### Data analysis

To assess the effectiveness of the implementation strategy, the proportion of patients that are treated in accordance with the guidelines before and after implementation of the guidelines in both the intervention and control hospitals will be measured. Medical outcome measures will include CS rates and maternal as well as neonatal complications related to vaginal delivery or CS. Multilevel multivariate analysis will be carried out to assess the independent effect of the implementation strategy on adherence to the CS quality indicators and medical outcome measures. A qualitative descriptive analysis will be done in order to evaluate the process. Furthermore, by means of a questionnaire, the experiences of healthcare providers and patient satisfaction with the implementation strategy will be evaluated, and the outcomes will be descriptive.

The costs analysis will be performed from a healthcare perspective. The costs of the implementation process will be calculated on the basis of the time and materials invested based on activity-based costing (ABC) approach, focusing on activities performed with costs accumulated at the activity level(s) of the healthcare implementation processes. The costs of implementation of the guidelines and consolidation consist of personnel and material costs. The input of resources will be assessed by collecting volumes of consumed resources, and multiplying these by the price of each resource unit. For collecting information on the input of the resources, registration forms will be completed by the people involved in the implementation and consolidation process. The prices of each resource unit will be based on standard costs [22], market prices, or self-determined costs. The medical costs used in de cost analysis will include CS rates and maternal and neonatal complications related to vaginal delivery or CS. The costs of implementation and costs of the changed medical care will be weighed against the proportion of patients that are treated according to the CS guideline, after implementation. The cost-effectiveness of implementation will be expressed as the incremental costs per extra patient treated according to the CS guideline, compared to the ‘do-nothing’ strategy (*i.e.*, no implementation, for which data before implementation will be used).

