### Controlled before-and-after study

#### Design and methods

Based on the results of the current care study and the barrier and facilitator study, one or more target groups for a tailor-made implementation strategy will be identified. Target groups will be selected with focus on women with both a high incidence of the indicator (our hypothesis is that this will include, for example, non-progressing labour and previous CS) and low indicator adherence. A tailor-made implementation strategy will be developed in order to increase adherence to the CS quality indicators. This strategy will be executed and evaluated in a clustered CBA study in 12 hospitals (six intervention, six control hospitals) (see sample size calculation) in terms of effectiveness, experiences, and costs. It is likely that a strategy with different implementation elements is needed because several barriers for implementation of recommendations may exist at different levels. This will probably result in a combined intervention directed at the level of professionals, patients, and the organisation.

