#### Study population and setting

The implementation strategy will be executed and evaluated in 12 hospitals (see sample size calculation) that also participated in the current care study: six intervention hospitals in which the newly developed strategy will be applied; and six control hospitals in which care as usual will be offered. In order to select these 12 hospitals, all 20 hospitals of the current care study will be categorized into university, non-university teaching, and non-university non-teaching hospitals (three categories). Within these three categories, possible hospital pairs will be made based on pre-intervention adherence to quality indicators and CS rates, as measured in the current care study. To get a sample representative for the Dutch setting, in total two university hospitals, six non-university teaching hospitals and four non-university, non-teaching hospitals will be asked to participate. Subsequently, the participating hospitals have to be assigned to the intervention and control group. This will be done per stratum and based on geographic region. The evaluation will include an effect, process, and cost analysis. Just as in de current care study, the effects will be measured both at medical outcome level (*i.e.,* CS rates and complication rates) and on guideline adherence level. Satisfaction with and applicability of the tailor-made implementation strategy for both patients and healthcare professionals will be measured in a process evaluation. Information regarding the process will be gathered in a qualitative study in the hospitals in which the implementation strategy was applied. Individual interviews will take place among the involved healthcare professionals and patients to gather data about experiences with the changed care. During the interview, they also will be asked about which elements of the tested strategy they specifically used to implement the evidence-based guidelines; how satisfied they are with the different elements; and their opinion about the feasibility of the different elements.

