Furthermore, a cost analyses of the tested implementation strategy will take place with respect to three aspects: 1) the rate at which the guideline recommendations are already applied; 2) the costs of the implementation strategy (taking into account the development of the strategy, training of healthcare professionals, and possible extra costs regarding both time and medical costs) and 3) the effectiveness of the implementation strategy. In order to measure the effectiveness of the implementation strategy both the effects on medical outcome (*i.e.*, CS rates, complication rates) and adherence to CS quality indicators will be measured. The cost-effectiveness of the implementation strategy will be expressed as the incremental costs per extra patient treated according to the CS quality indicators, compared to the ‘do-nothing’ strategy.

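### The cost-effectiveness ratio takes do-nothing from pre-implementation data, although concurrent usual-care hospitals are measured and define the study's own effect

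*Protocol article*

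**What the plan says.** All references are to the protocol article, part Controlled before-and-after study, unless stated otherwise.

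- **Comparator.** Data analysis equates do-nothing with "no implementation, for which data before implementation will be used". It also says that the costs of implementation and of changed care "will be weighed against the proportion of patients that are treated according to the CS guideline, after implementation".
- **Ratio.** Study population and setting: "The cost-effectiveness of the implementation strategy will be expressed as the incremental costs per extra patient treated according to the CS quality indicators", again against do-nothing. Data analysis repeats it with guideline in place of quality indicators: "The cost-effectiveness of implementation will be expressed as the incremental costs per extra patient treated according to the CS guideline".
- **Controls.** Study population and setting provides for "six control hospitals in which care as usual will be offered". Under Data analysis, the proportion treated in line with the guidelines "before and after implementation of the guidelines in both the intervention and control hospitals will be measured".
- **Effect.** Outcome measures defines the primary outcome as the increase in adherence between intervention and control hospitals, together with CS rates in both groups. Costs are listed among the secondary outcomes.
- **Inputs to the cost analysis.** Study population and setting names three: how far the recommendations are already applied, what the strategy costs, and how effective it is.
- **Choice of target.** Design and methods: "Target groups will be selected with focus on women with both a high incidence of the indicator". The same sentence adds low adherence as the second criterion.

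**The concern.** Hospitals that deliver usual care over the same period are the natural do-nothing arm. A comparison with earlier data equals a comparison with no implementation only if nothing else would have changed in the meantime. The article gives reason to doubt that. Its Background reports a rising CS rate, and CS rates enter the medical costs. The target group is also chosen partly for low adherence, which can lead to some rebound on re-measurement without any strategy.

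At stake is the agreement between two results of one study. The controlled analysis could show a small effect beside a favourable cost per additional adherent patient, or the reverse. The Abstract presents costs as one of three aspects on which the strategy is tested, so readers will use this ratio.

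**Working it through.** The article states no cost-effectiveness figure, effect size or follow-up interval for this study, so there is nothing to reproduce. The only input from the document is the CS trend. Every other value below is an assumption.

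**1. Adherence (denominator).** Let E be the true gain in percentage points and s the background change, including any regression to the mean.
- Before-after change = E + s.
- Intervention-versus-control difference in change = E, if s is the same in both groups.
- With incremental cost held fixed, before-after ratio ÷ controlled ratio = E / (E + s).

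| Assumed E | s = -3 | s = 0 | s = +2 | s = +5 |
|---|---|---|---|---|
| 5 | 5/2 = 2.50 | 1.00 | 5/7 = 0.71 | 5/10 = 0.50 |
| 10 | 10/7 = 1.43 | 1.00 | 10/12 = 0.83 | 10/15 = 0.67 |
| 15 | 15/12 = 1.25 | 1.00 | 15/17 = 0.88 | 15/20 = 0.75 |

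A value below 1 means that the strategy looks cheaper per additional adherent patient than it is.

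**2. CS rate (medical-cost part of the numerator).** The Background gives a rise from 8.1% to 13.6% over a decade: (13.6 - 8.1)/10 = 0.55 points a year if linear. This is the national overall rate; the target group's trend is not given. Applied over an assumed interval to an assumed true effect of -2.0 points, the before-after change would be:
- 1 year: -2.0 + 0.55 = -1.45
- 2 years: -2.0 + 1.10 = -0.90
- 3 years: -2.0 + 1.65 = -0.35

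The background rise hides part of the CS saving and so adds medical cost to the strategy's account. No unit prices are given, so this cannot be turned into money.

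**3. Regression to the mean.** This applies only if the before data are the data used to choose the target. A simulation (20,000 runs per setting) picked the lowest observed of K indicators around a mean true adherence of 75%, the value assumed in the current-care sample size. It assumed K = 5 to 20, 30 to 300 eligible women per indicator and a between-indicator SD of 0 to 10 points. The expected rebound was about 0.8 to 15 points; with K = 10, 100 women and an SD of 5 to 10 points it was 3.1 to 4.7. It shrinks as the number of eligible women grows.

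**4. Both parts together.** A positive s enlarges the denominator and lowers the ratio. A rising CS rate enlarges the numerator and raises it. Neither size is known for the target group, so the sign of the net bias is open.

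**The case against.** The strongest reply has four parts.

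- **Costs are secondary.** The primary effect is a controlled contrast with multilevel analysis, and the comparator does not touch it. Implementation time and materials are recorded directly and are not distorted either. This stands, and it limits the weight of the point.
- **The controls may not be dropped.** A reader might infer that the economic analysis ignores the control hospitals altogether. The documents do not support that. The strategy's effectiveness is a named input to the cost analysis, and Outcome measures defines effectiveness between groups. So the sections are in tension, and the explicit definition of do-nothing needs to be reconciled with the rest. Nor does the text say whose before data are meant. The intervention hospitals' own data are the natural reading, but data pooled over all hospitals would carry the same flaw.
- **Regression to the mean is conditional.** Study population and setting uses current-care values as pre-intervention values when pairing hospitals, but nothing states that the before measurement in the cost analysis is that same dataset. Selection also favours high incidence, which means larger denominators and less rebound. Hospitals are paired on baseline adherence, not selected for low values.
- **No single size or direction holds.** A reader might infer that the strategy will be made to look more cost-effective than it is, by a definite factor. Any such factor rests on an invented change in the control hospitals with cost held fixed; negative drift reverses it, and the CS trend works against it. Nor can the national 0.55 points a year be converted into extra CS in the costed group.

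What remains is the stated comparator itself. It is a written rule, not a detail left to a fuller document.

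**Conclusion.** The point holds as a should-fix on a secondary outcome. The plan fixes a historical comparator for the cost-effectiveness ratio while it measures a concurrent one and defines its effect by it. The two agree only if the background changes in adherence and in the costed outcomes are zero or happen to cancel. The national CS trend suggests that drift in a costed outcome is not zero, although the target group's own trend is unknown.

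The size cannot be derived from the document. The factor of 1.43 to 0.67 is an illustration that rests on an assumed 10-point gain, fixed incremental cost and drift of -3 to +5 points. The net direction is indeterminate.

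**What to change.** In the Data analysis section, define do-nothing by the concurrent control hospitals:

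- **Denominator:** the intervention-versus-control difference in change in adherence, from the multilevel model already planned.
- **Numerator:** implementation costs plus the intervention-versus-control difference in change in medical costs (CS and complications).
- **Sensitivity analysis:** the before-only comparison, stating which hospitals and which dataset supply the before data.

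Reword the sentence that weighs costs against adherence after implementation so that it refers to the same contrast.

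This is a change of wording. Adherence, CS rates and complications are already to be measured in this study, with before and after data planned in both groups, so no new clinical data are needed. The price is a less precise ratio from 12 hospitals. Assignment is described as per stratum and by geographic region, not as random, so the change removes only drift that both groups share.

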#### Ethical considerations

The Medical Ethical Committee (CMO) of Maastricht (azM/UM) approved this study protocol and declared that no ethical approval was necessary (MEC 09-4-047).

## Discussion

The CS rate in The Netherlands is comparatively low compared to other countries, but it is increasing especially in the group of healthy women with a singleton pregnancy in vertex position at term. One would expect this to coincide with improved outcomes for mothers and children, which is, however, not the case [5]. Although many suggestions considering the reason for this rise have been made, the answer is not yet clear. We hypothesize that incomplete guideline adherence is a possible cause for the current increase in CS rate. In this study we will determine current Dutch care regarding CS using quality indicators. We will use national as well as international guidelines to select the recommendations, resulting in at least a set of internationally accepted indicators. Because we will also report the current CS rates by classification into the internationally accepted Robson Criteria, international comparison of incidences of CS rates in different subgroups will be possible. In that way, specific indicators and incidences of those indicators might be applicable elsewhere. Furthermore, we will focus on factors that influence guideline implementation, and thus optimal care in the barrier and facilitator analysis.

Although earlier reviews claimed that multifaceted strategies (combinations of many different interventions) are often effective, Grimshaw found that a higher number of intervention components was not related to higher effectiveness [23]. It seems plausible that combined interventions are only more effective than single interventions, if these are addressed at the specific barriers to change. This is also the conclusion of Chaillet *et al*.: in the obstetric setting in general and the CS setting in particular, prospective identification of efficient strategies and barriers to change is necessary to achieve a better adaptation of intervention and to improve clinical practice guideline implementation [24].

This study will hopefully result in one or more target groups with high incidence and low guideline adherence and the evaluation of an implementation strategy to improve care. For example, non-progressing labour is known to be one of the major reasons to perform a CS. Should guideline adherence in these women be low, an intervention based both on informing women and reminders on optimal care for caregivers could be an option. Another possible target group might be women with a previous CS. Although in general, the VBAC rate was previously reported higher in the Netherlands than in some other countries, recent data are lacking. Improvement of care for these women could consist of a decision aid to improve counselling. Both types of interventions are also possibly effective outside the Netherlands. The ultimate aim of our study is to implement the national and international evidence-based guidelines on CS in all Dutch hospitals in order to reduce the incidence of CS and improve the outcome for mother and child. Furthermore, this study provides a framework for future studies to enable improvement of guideline adherence and reduction of the CS rate.

## Abbreviations

ACOG: American College of Obstetrics and Gynecology; CS: Caesarean section; NGC: National Guideline Clearinghouse; NICE: National Institute of Clinical Evidence; NVOG: Dutch Society of Obstetrics and Gynaecology; RCOG: Royal College of Obstetricians and Gynaecologists; SOGC: Society of Obstetricians and Gynaecologists of Canada.
